### Preoperative examinations

Once the candidate is qualified, the informed consent will be signed. The baseline characteristics of all the candidates, including family history, smoking history, comorbidity, symptoms and signs, would be collected. Before surgery, those qualified patients will take full preoperative examinations and evaluations, including chest CT, abdominal CT or ultrasound, cervical ultrasound examinations. Head magnetic resonance imaging (MRI) and positron emission tomography/computed tomography (PET.CT) are also preferred for the prevention of cancer metastasis, especially for patients with clinical T1b NSCLCs. Besides, preoperative pulmonary function examination as well as serum tumor markers will also be tested before surgery. In addition, each patient will receive simplified bedside pulmonary function examination the day before operation. All the preoperative examination and evaluation data will be entered into an investigator initiated trial Electronic Data Capture (IIT-EDC) System (Taimei Technology, Zhejiang Province, China) an electronic data collection system.

### Randomization

Central randomization will be performed and the patients will be randomized in a 1:1 ratio to either a minimally invasive anatomical segmentectomy group or a minimally invasive lobectomy group. Randomization will take place the day before surgery through a Central Randomization System based on the IIT-EDC.

### Surgery

Minimally invasive thoracic surgery including both VATS and RATS is required for this trial, including single-port, two-port, three-port or four-port incisions without rib spreading. Lobectomy and segmentectomy should be anatomically resected. The hilar structures should be separated and pulmonary vessels and bronchus should be divided respectively. Lobar fissure and intersegmental plane should be managed either by stapler alone or by stapler together with energy devices. Both segmentectomy and lobectomy groups should receive systemic lymph node dissection or sampling according to the NCCN guidelines (5).

Intraoperative frozen pathology is required for the resected specimen, including the pulmonary surgical margin of segmentectomy. If the segmental resection margin is positive of malignancy on frozen section, segmentectomy should be converted to lobectomy. All the intraoperative data including intraoperative complications will be carefully recorded. In addition, preoperative imaging, peripheral blood sample and intraoperative tumor specimen of each patient will also be collected for further exploratory research (**Figure 1**).

**Figure 1 f1:**
[figure not shown]
The study flowchart of the Ground Glass Opacity Resection Extent Assessment Trial (GREAT).

### Postoperative managements

After surgery, digital drainage is preferred for chest drains to record the degree of airleak. Re-expansion of the residual lung will be calculated on chest X-ray on the first postoperative day (POD1) (**Figure 2**). Simplified bedside pulmonary function examination will be repeated on POD2. During the postoperative in-hospital interval, all the postoperative information along with complications will be recorded. The Common Terminology Criteria for Adverse Events (CTCAE) version 5.0 is used for determining postoperative complications where the severity ≥2 is considered as the occurrence of postoperative complications. Specifically, the definition of prolonged air leak is considered as air leak ≥5 days after pulmonary resection.

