### Follow-up

Each qualified patient after surgical resection should take postoperative follow-up in out-patient department. Within the first month after operation, patient will receive chest X-ray examination to assess the extent of residual lung expansion after radical resection. Pulmonary function examination *via* spirometry test will be performed in each participant at 6 months after surgery. In the first three years after surgery, patients need to receive chest CT scanning, neck and abdomen ultrasound examination and serum tumor markers every six months. Thereafter, the above examinations need to be repeated once a year until the fifth year after operation. All follow-up information is carefully recorded.

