### Study endpoints

The primary endpoint is 5-year recurrence-free survival (RFS), calculated from the date of surgery to the date of cancer recurrence or patient death or the last follow-up. The secondary endpoints are 5-year overall survival (OS), perioperative outcomes and pulmonary function preservation. OS is calculated from the date of surgical resection to the date of patient death or the last follow-up. Perioperative outcomes include blood loss, operation time, morbidity rate, mortality rate, chest drain duration, length of hospital stay, and residual lung re-expansion. Pulmonary function change will be evaluated on short-term (the second day after surgical operation) and on long-term (6 month after operation) after surgery. 5% difference in FEV1 at 6 months after surgery is set as the secondary end point between the segmentectomy and the lobectomy groups. Exploratory research includes prediction of histological subtypes on preoperative imaging using artificial intelligence (AI). We also try to explore the characteristics of gene mutation status *via* next-generation sequencing (NGS) among GGO-containing early-stage NSCLCs.

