### Statistical analysis

A two-sided *p*<0.05 is set as a statistical difference. Pearson χ^2^ or Fisher’s exact test and Student t test are performed for the comparison of baseline characteristics, perioperative outcomes and the pulmonary functions. Comparisons of OS and RFS between minimally invasive segmentectomy and lobectomy groups are all estimated by Kaplan-Meier method and testified by the two-side Log-rank test. Cox proportional hazard regression model will be used to evaluate the hazard ratio of minimally invasive segmentectomy group and minimally invasive lobectomy group for OS and RFS, respectively. Subgroup analyses will also be performed by total lesion size ≤ 2cm or 2cm-≤3cm. Intention to treat analysis (ITT) will be performed for all enrolled patients. Per protocol analysis (PP) will be performed for patients who have completed the trial in compliance with the protocol.

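### Complication recording is tied to the hospital stay, which is itself an open-label outcome, so if stay differs by arm the morbidity comparison can favour the arm discharged earlier

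*Protocol article*

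**What the plan says.** All references are to the protocol article.

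- **Recording period (Postoperative managements):** "During the postoperative in-hospital interval, all the postoperative information along with complications will be recorded".
- **What counts (same section):** complications are graded by CTCAE version 5.0, "where the severity ≥2 is considered as the occurrence of postoperative complications". No number of days is attached.
- **Endpoints (Study endpoints):** "Perioperative outcomes include blood loss, operation time, morbidity rate, mortality rate, chest drain duration, length of hospital stay, and residual lung re-expansion". Morbidity, mortality and length of stay thus stand side by side as secondary outcomes, and neither rate has a time window.
- **After discharge (Follow-up):** "Within the first month after operation, patient will receive chest X-ray examination to assess the extent of residual lung expansion after radical resection". Spirometry follows at 6 months, with periodic imaging and tumour markers to year five. The section ends: "All follow-up information is carefully recorded". Complications are not named.
- **Deaths (Study endpoints):** "OS is calculated from the date of surgical resection to the date of patient death or the last follow-up". Death is also an event for recurrence-free survival.
- **Analysis (Statistical analysis):** chi-square or Fisher tests and t tests "are performed for the comparison of baseline characteristics, perioperative outcomes and the pulmonary functions".
- **Use (Abstract and Conclusions):** once the survival conditions are met, better perioperative outcomes are one of two alternative grounds for preferring segmentectomy. Better preserved lung function is the other.

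**The concern.** A recording period that ends at discharge has a different length for each patient. Here that length is also an outcome the trial compares, and staff who know the allocation decide when it ends. One secondary outcome therefore sets the observation time for another. A crude comparison of proportions makes no allowance for this.

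The trial aims to show that segmentectomy lowers perioperative risk. If segmentectomy patients leave earlier, part of any recorded morbidity advantage could come from shorter observation rather than fewer complications. That advantage could then support the recommendation described in the Conclusions. Separately, complications that first appear at home would be missing from both arms, so the absolute rates would be too low whatever the difference in stay.

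**Working it through.** The plan gives no complication rate, onset time or length of stay, so it has no figure to reproduce. The check is a reading of the sections, followed by an illustration on assumed inputs.

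**Reading**

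1. The only period stated for recording complications is the hospital stay.
2. The first-month X-ray has lung expansion as its stated purpose. The later visits are spirometry, imaging and tumour markers. None is described as a complication assessment.
3. Deaths after discharge are collected with dates through the survival endpoints, so a fixed-day mortality rate can be derived. What is missing is a statement of whether the perioperative rate is in-hospital or fixed-day.
4. The planned tests do not adjust for time observed.

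**Illustration**

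*From the document:* 1024 patients randomised 1:1, so 512 per arm; two-sided 0.05.

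*Assumed:* the same true 30-day risk p of a grade 2 or higher complication in both arms; exponential onset with mean m days; every patient in an arm discharged on day L; events counted only up to L.

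Recorded rate = p × (1 − exp(−L/m)).

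With p = 20%, m = 4, and L = 4 v 5:

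- Shorter-stay arm: 0.20 × (1 − exp(−1)) = 0.20 × 0.632 = 12.6%
- Longer-stay arm: 0.20 × (1 − exp(−1.25)) = 0.20 × 0.713 = 14.3%
- Spurious difference: 1.63 percentage points
- Standard error: √[(0.126 × 0.874 + 0.143 × 0.857)/512] ≈ 2.1 points, so the shift is 1.63/2.13 ≈ 0.76 standard errors
- Chance of a significant result favouring the shorter-stay arm: P(Z > 1.96 − 0.76) ≈ 0.116, against 0.025 nominal

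Two grids of assumptions:

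| p | m (days) | L (days) | Spurious difference (points) | Chance of false significance |
|---|---|---|---|---|
| 15–30% | 3–6 | 4 v 5, 5 v 6, 5 v 7 | 0.8–3.7 | 6–33% |
| 10% or 20% | 3, 5 or 8 | 4 v 5, 4 v 6, 5 v 7 | 0.7–3.0 | 6.5–33% |

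The second grid truncates onset at 30 days by dividing by 1 − exp(−30/m). One example from it is p = 20%, m = 5, L = 4 v 6: recorded rates of 11.0% v 14.0%, and a false-significance chance of about 30%.

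**Limits of the model:** if L is the same in both arms, the difference is 0 and the chance returns to 2.5%. The same holds for any fixed period applied equally to both arms.

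**The case against.** The strongest reply has four parts.

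- **The text does not say that recording stops at discharge.** This is a condensed article, its electronic forms are not shown, and follow-up information is said to be recorded. A reader might infer an express rule against later recording, and the document does not support that. What stands is that the article does state a period, that this period is the stay, and that nothing it names after discharge is a complication assessment. The point is about a stated rule, not a missing detail.
- **Deaths are captured.** A reader might infer that mortality will also look lower in the arm discharged sooner. The survival endpoints run from surgery to death, so deaths after discharge are in the data. Only the undefined window remains as a fault.
- **Air leak.** The article also says "the definition of prolonged air leak is considered as air leak ≥5 days after pulmonary resection". A reader might see a contradiction, since a patient sent home before day 5 with a leak could not be classified from ward data. No section describes such discharges, the definition counts from surgery, and drain duration is itself an outcome. No contradiction is shown.
- **The figures are assumed, and the model leans towards bias.** Patients with a developing problem tend to be kept in, so risk just after discharge is probably lower than an exponential onset implies. This is a fair criticism, and the figures show only how the mechanism works.

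**Conclusion.** The point holds for morbidity. As written, the plan ties complication recording to a period that can differ by arm and then compares the rates crudely. If stay differs, the earlier-discharged arm has an advantage unrelated to its true risk. Post-discharge complications are missed in both arms regardless.

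The size cannot be derived from the documents. Under the assumptions shown it is roughly 1 to 4 percentage points; it may be smaller if discharge depends on clinical state, and it is zero if stay does not differ. For mortality, the plan needs only a stated window.

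The consequence is limited. The primary endpoint is untouched, morbidity is one of seven listed perioperative outcomes, and preferring segmentectomy first requires non-inferior recurrence-free and overall survival. The change is still worth making early, because complications not collected when they occur are hard to recover later.

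**What to change.** - Define morbidity and perioperative mortality over one fixed period from surgery, identical in both arms and regardless of where the patient is. Thirty days is an example; the document gives no figure.
- Collect post-discharge complications at the first-month contact that already exists. That contact is currently only somewhere within the first month, so it may come before day 30. Either time it at or after the end of the period, or set the period to match the contact.
- Take deaths from survival follow-up.
- Report in-hospital rates as supplementary.

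**Cost:** a wording amendment, a complication form at the existing contact if the current forms lack one, and a minor constraint on when that contact takes place. Recorded rates will be slightly higher in both arms, and some post-discharge events will rest on patient report.

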**Figure 2 f2:**
[figure not shown]
The collapse rate of lung after operation.

### Pathological evaluation

Pathological examinations include intraoperative fast frozen evaluation and postoperative final pathology examination. For frozen section, the resected specimen, the margin of resected bronchus and the pulmonary surgical margin of segmentectomy will be assessed during surgical operations by an experienced pathologist. Specially, for the pulmonary surgical margin of segmentectomy, the shortest distance between the tumor and the pulmonary surgical margin should be measured. In the final pathology, routine examinations should at least include number of tumors, tumor location, tumor size, pathological types and subtypes, status of pleural invasion (PI), status of lymphovascular invasion (LVI), status of spread through air spaces (STAS), numbers of resected lymph nodes and lymph node stations. Histological subtypes and subtype percentage of invasive adenocarcinoma should be all presented according to the World Health Organization (WHO) classification of lung tumors (12, 13). Gene mutations test by next-generation sequencing is encouraged for each participant.

### Postoperative adjuvant therapy

Whether postoperative adjuvant therapy is necessary will be evaluated by thoracic surgeons according to the final pathology of each patient. For patients with pathological stage IA NSCLC, routine follow-up strategy is recommended. For patients with pathological stage II-IIIA NSCLC and high-risk stage IB NSCLC (such as those with solid or micropapillary component, PI, LVI, STAS, etc.), platinum-based chemotherapy is recommended. Adjuvant targeted therapy and immunotherapy can also be considered for well-selected pathological stage IB-IIIA NSCLC patients.

### Follow-up

Each qualified patient after surgical resection should take postoperative follow-up in out-patient department. Within the first month after operation, patient will receive chest X-ray examination to assess the extent of residual lung expansion after radical resection. Pulmonary function examination *via* spirometry test will be performed in each participant at 6 months after surgery. In the first three years after surgery, patients need to receive chest CT scanning, neck and abdomen ultrasound examination and serum tumor markers every six months. Thereafter, the above examinations need to be repeated once a year until the fifth year after operation. All follow-up information is carefully recorded.

### Study endpoints

The primary endpoint is 5-year recurrence-free survival (RFS), calculated from the date of surgery to the date of cancer recurrence or patient death or the last follow-up. The secondary endpoints are 5-year overall survival (OS), perioperative outcomes and pulmonary function preservation. OS is calculated from the date of surgical resection to the date of patient death or the last follow-up. Perioperative outcomes include blood loss, operation time, morbidity rate, mortality rate, chest drain duration, length of hospital stay, and residual lung re-expansion. Pulmonary function change will be evaluated on short-term (the second day after surgical operation) and on long-term (6 month after operation) after surgery. 5% difference in FEV1 at 6 months after surgery is set as the secondary end point between the segmentectomy and the lobectomy groups. Exploratory research includes prediction of histological subtypes on preoperative imaging using artificial intelligence (AI). We also try to explore the characteristics of gene mutation status *via* next-generation sequencing (NGS) among GGO-containing early-stage NSCLCs.

### Sample size calculation

Expected 5-year RFS is 91% according to a previous study at Shanghai Chest Hospital (6). With a one-sided alpha error of 5% and at least 80% power and a non-inferiority margin of 5% along with a drop-out rate of 5%, the sample size of this study requires 1024 patients.

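### The primary non-inferiority comparison is sized at one-sided 5%, but the only level and test the analysis section gives for RFS are two-sided 5% and a log-rank test of difference; carried to the margin, that level leaves power below 80%

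*Protocol article*

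**What the plan says.** The Sample size calculation section sizes the trial "With a one-sided alpha error of 5% and at least 80% power". It assumes 5-year RFS of 91%, a non-inferiority margin of 5% and 5% drop-out, and concludes that "the sample size of this study requires 1024 patients". It names no formula.

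The Statistical analysis section opens with a general rule: "A two-sided *p*<0.05 is set as a statistical difference". It then says that OS and RFS comparisons between the arms "are all estimated by Kaplan-Meier method and testified by the two-side Log-rank test", and adds a Cox model for the hazard ratio. It does not mention the margin, a confidence interval, a one-sided test or a separate level for the primary comparison.

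The Abstract and the Conclusions make the recommendation of segmentectomy depend on non-inferiority in 5-year RFS.

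**The concern.** A one-sided 5% non-inferiority test passes when the two-sided 90% interval for the difference stays inside the margin. A two-sided 5% level corresponds to a 95% interval, which is one-sided 2.5% in the non-inferiority direction. The article sizes on the first. The only level it attaches to RFS in the analysis is the second.

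Two things are at stake. The chance of a false claim of non-inferiority is 5% under one section and 2.5% under the other, so some results would pass by one rule and fail by the other. And if the stricter level governs the primary decision, the power statement no longer describes the test that will be run.

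**Working it through.** **Inputs.** From Sample size calculation: RFS 91%, margin 5% (read as absolute, so the boundary is 86%), drop-out 5%, N = 1024. From Randomization: "the patients will be randomized in a 1:1 ratio". From Follow-up: "Thereafter, the above examinations need to be repeated once a year until the fifth year after operation", so events are counted to five years. Evaluable patients: 1024 × 0.95 = 972.8, or 486.4 per arm. Normal quantiles: 1.645 (one-sided 5%), 1.960 (one-sided 2.5%), 0.842 (80% power).

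**Reproducing 1024 at one-sided 5%.** Three formulas were tried:

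- *A. Risk difference, 91% in both arms.* Per arm: 2 × 0.91 × 0.09 × (1.645 + 0.842)² / 0.05² = 405.1, rounded up to 406. Total 812, or 855 with drop-out. This does not reproduce 1024.
- *B. Unpooled variances, 91% vs 86%.* Per arm: (0.0819 + 0.1204) × (1.645 + 0.842)² / 0.05² = 500.3. Total about 1001, or 1053 with drop-out. Within 3% of 1024.
- *C. Schoenfeld.* The hazard ratio at the margin is ln 0.86 / ln 0.91 = 1.599, with log 0.4695. Events: 4 × (1.645 + 0.842)² / 0.4695² = 112.2. Dividing by the mean event risk (9% + 14%)/2 = 11.5% and by 0.95 gives 1027, or 1034 if each step is rounded up. Within 1% of 1024.

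The stated total is therefore consistent with one-sided 5% and about 80% power under B or C.

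**Power of the planned trial at each level.** Power is Φ(signal − z):

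- A: signal = 0.05 / √(0.1638 / 486.4) = 2.725
- B: signal = 0.05 / √(0.2023 / 486.4) = 2.452
- C: 972.8 × 0.115 = 111.9 events; signal = 0.4695 × √111.9 / 2 = 2.483

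| Formula | One-sided 5% (90% CI) | One-sided 2.5% (95% CI) | N for 80% at one-sided 2.5%, with drop-out |
|---|---|---|---|
| A | 86.0% | 77.8% | 1085 |
| B | 79.0% | 68.9% | 1337 |
| C | 79.9% | 70.0% | 1309 |

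With no drop-out at all (512 per arm), formula A gives 79.8% at one-sided 2.5%.

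**Where the two rules disagree.** Under A the standard error is 1.84 points. The 90% rule passes an observed segmentectomy deficit up to 5 − 1.645 × 1.835 = 1.98 points. The 95% rule passes one up to 5 − 1.960 × 1.835 = 1.40 points. If the arms are truly equal at 91%, the chance of a result that passes one rule and fails the other is 86.0% − 77.8% = about 8%.

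**The case against.** The strongest reply is that the sections can be read as compatible. The two-sided threshold is worded as a criterion for a statistical difference and would naturally cover baseline, perioperative and lung-function comparisons. The section never sets a 95% interval against the margin. The only alpha tied to non-inferiority is the one-sided 5% in Sample size calculation, and at that level the power is essentially as stated. This stands, and it makes the shortfall conditional. It does not remove the mismatch, because the analysis section names RFS, the primary endpoint, as tested two-sided and makes no exception.

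The size of the shortfall also depends on a formula the article does not name: about 2 points below 80% under A, about 10 under B and C. Nor is the origin of 1024 certain. Formula A at one-sided 2.5% needs 1030 before drop-out. A Schoenfeld calculation assuming three years of accrual and at least five years of follow-up, with events counted beyond year five, gives 1027 at one-sided 2.5%. That variant is set aside because the endpoint and the follow-up schedule end at five years and the article states no accrual period.

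Three stronger readings are tempting but not supported:

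- *The trial is underpowered.* This follows only if non-inferiority is decided at one-sided 2.5%, which no section says.
- *The type I error is inflated.* Neither level exceeds the declared 5%.
- *Hazard-ratio power proves the case.* With 9% event risk in both arms (about 88 events), power is 71% at one-sided 5% and 59% at one-sided 2.5%. The first figure is already below 80% at the design's own level, so that gap concerns effect scale and event count, not sidedness.

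The full protocol or analysis plan may hold the decision rule. The point here is that two stated levels differ, not that detail is absent.

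**Conclusion.** The inconsistency is real and lies in the stated text: one-sided 5% for sizing the primary comparison, against two-sided 5% and a test of difference as the only analysis given for RFS. A log-rank test of difference does not by itself assess a 5-point margin, so the analysis section as written does not carry out the design's test.

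If the two-sided level is carried to the non-inferiority decision, the stated power is not met under any of the five-year formulas A to C: about 69–78%, against about 79–86% at one-sided 5%. These figures assume an absolute 5-point margin, true RFS of 91% in both arms for A, 91% vs 86% as planning values for B and C, and 5% drop-out. Neither 86% nor 78% should be taken as the trial's power, because formula A does not recover 1024.

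**What to change.** In Statistical analysis, state that the primary test is non-inferiority of 5-year RFS against the 5-point margin at the design's one-sided 5%. Judge it by the two-sided 90% interval for the Kaplan-Meier difference at five years, with the 95% interval also reported. Confine two-sided p<0.05 and the log-rank test to comparisons of difference or superiority. Name the sample size formula.

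If the sponsor instead chooses one-sided 2.5%, change the level in Sample size calculation too, keep 1024, and restate power as below 80% (about 69–78%, depending on the named formula).

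The cost is a sentence or two in each section. No patients, visits or procedures change under either choice; the second carries a less favourable power statement.
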